### Online intervention platform

The technology platform used to deliver the ICare Prevent intervention is provided by Minddistrict. This company is full partner of the ICare project consortium and responsible for the provision and maintenance of the platform. Its content management system is used to upload the interventions, add new participants and eCoaches, as well as questionnaires. Access to the platform is provided by means of email and personalized password combination. It is currently used both in clinical research and in routine practice to provide guided and unguided self-help interventions for a variety of mental health conditions. The platform conforms to all required quality standards and operates according to the ISO 27000 and NEN 7510 norms. All data are securely stored on ISO 27000 certified servers and transmitted using HTTPS with SSL certificates (AES-256 and SHA-1, 2048-bit RSA). Unauthorized access to the platform is therefore not possible. A data management and safety plan has been developed as part of the larger ICare project.

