### Intervention

ICare Prevent is an Internet-based intervention with mobile-support by means of an application (app). It uses both transdiagnostic and individually tailored components that are based on previously developed Internet-based modules, all using evidence-based CBT principles [47–51]. ICare Prevent consists of seven main sessions and one booster session. Participants are advised to complete one main session per week. The intervention contains text, exercises, images, explanatory videos, as well as audio files and downloadable information. Testimonials are used to illustrate (homework) exercises. The main sessions follow the same basic structure. First, the content of the current session is explained, followed by a review of the homework exercises from the previous session. In accordance with the individually tailored approach of the intervention, participants can choose content depending on their predominant complaints, i.e. depression or anxiety. For example, in the fifth session, participants can either practice problem-solving or exposure techniques. The content per session is summarized in Table 1. Throughout sessions 2–7, participants can choose to complete one of eight choice modules following the main intervention content. In accordance with the transdiagnostic approach of the intervention, these modules aim at increasing resilience and tackle problems common to both depression and anxiety. In addition, five diaries with different content, such as positive activities and sleep, are accessible through the online platform and the app. An overview of all choice modules and diaries is given in Table 2.

**Table 1 Tab1:** Overview of topics covered by the intervention per session

Session	Topic
1	Introduction, technical aspects, goal-setting, and behavioral activation in the context of basic psychological needs and important personal values
2	Identifying problems and tackling them through behavioral activation
3	Psychoeducation on depression and anxiety
4	Cognitive restructuring and challenging negative thoughts
5	Identifying the most prominent complaints and accordingly follow either:
	a) problem-solving strategies for more prominent depressive complaintsb) exposure strategies for more prominent anxiety complaints
6	Deepening the training on the route chosen in session 5
7	Making a plan for the future
8	Booster session (four weeks after session 7)

**Table 2 Tab2:** Overview of topics covered by the choice modules and diaries

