### Care as usual (CAU)

Participants in all three conditions may use CAU services. We monitor healthcare services used, as well as other means to alleviate symptoms (e.g. as talking with relatives and friends), by means of a self-report questionnaire, the Client Service Receipt Inventory (CSRI; [52]). In the Netherlands, CAU for subclinical symptoms of depression and/or anxiety can include visits to the general practitioner, making use of support staff trained in the provision of help for mild psychological symptoms, or (student) psychologists according to Dutch guidelines [53, 54]. Alternatives include homeopaths, alternative medicine providers, or self-medication. Participants in the control group will receive access to ICare Prevent one year after trial inclusion.

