### Statistical analysis

All analyses for the primary and secondary outcomes will be based on multilevel mixed model regression analyses for continuous outcomes in order to assess change over time. Time will be used as a predictor variable and baseline measures will be included as covariates. Linear models will be used for normally distributed data and negative binomial models for left-skewed data. All analyses will be performed on an intention-to-treat (ITT) sample. Per-protocol analyses including only participants who conformed to their group allocation will be performed in addition. Missing data will be handled using either multiple regression imputation techniques if appropriate or full information maximum likelihood estimation [106]. The secondary outcome, time to mental health disorder onset during 12 months follow-up in all conditions, measured by the M.I.N.I., will also be compared using survival curve analysis. The curves will be compared using cox proportional hazard regression analysis using baseline symptom severity as a covariate. Hazard ratios will be calculated as measure of the effect size of group differences. Within secondary analyses, interactions with predictors will be added to the model in order to identify risk and protective factors.

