### Strengths and limitations

To our knowledge, this is the first trial that investigates the (cost-)effectiveness of a transdiagnostic individually tailored Internet-based intervention for the prevention of depression and anxiety in a college student population. Data on both symptom reduction as well as the time to onset of a mood or anxiety disorder will be measured. Although some research suggests that Internet-based interventions have the potential to be cost-effective compared to no treatment, no data are available for preventive transdiagnostic individually tailored Internet-based interventions for college students. Specifically, the added (economic) value of support by means of an eCoach needs to be closely monitored in the context of this low-intensity intervention.

Some possible limitations of the present trial should be noted. First, the sample size of this trial conducted among Dutch college students is insufficient for directly comparing the guided and unguided treatment arm as well as analyzing the time to a mental health disorder onset. Similarly, analyses of moderators and mediators will be underpowered and may therefore provide only limited insights. To counter this issue, data from all participating trials in the ICare project will be pooled in order to achieve enough statistical power. Second, an evaluation of societal costs might be difficult due to the fact that most students are seldom in full-time employment. The detrimental effect of depression and anxiety on absenteeism and presenteeism in the context of employment is therefore difficult to quantify. In order to increase the validity of the results, we have adapted the cost-effectiveness questionnaire (CSRI; [52]) to fit the specifics of a student population by focusing on absenteeism and presenteeism in student jobs, as well as in lectures. Finally, previous research has shown that adherence to Internet interventions is a point of concern, especially in unguided formats [111, 112]. A series of automatic motivational messages and reminders will be used in order to increase adherence in the unguided study arm and we will closely observe factors related to dropout. This will be beneficial in designing future interventions and improving uptake of intervention content.

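### The additional per-protocol analysis will drop participants almost only from the two active arms, so its contrasts with CAU are not between randomized groups and are likely to favour the intervention

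*Protocol article*

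**What the plan says.** The Statistical analysis section of the protocol article makes ITT the main basis: "All analyses will be performed on an intention-to-treat (ITT) sample". It then adds: "Per-protocol analyses including only participants who conformed to their group allocation will be performed in addition". No adjustment for selection into that set is described.

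What conforming can mean differs by arm.

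- **CAU.** The section on care as usual says: "Participants in all three conditions may use CAU services". The range is wide: "Alternatives include homeopaths, alternative medicine providers, or self-medication". Nothing is required or forbidden. On the programme itself: "Participants in the control group will receive access to ICare Prevent one year after trial inclusion". The Online intervention platform section adds: "Unauthorized access to the platform is therefore not possible".
- **Guided and unguided.** There are seven main sessions and a booster, and the Intervention section says: "Participants are advised to complete one main session per week". Under Strengths and limitations the authors note that "adherence to Internet interventions is a point of concern, especially in unguided formats".

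**The concern.** A per-protocol set keeps the arms comparable only if the same kind of person is removed from each. Here the active arms have something a participant can fail to do, and the control arm has next to nothing. Active-arm participants who stop are removed, while the controls who would have stopped had they been offered the programme stay in.

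Students who keep up with sessions are likely to differ from those who stop in motivation and prognosis. The per-protocol difference from CAU would then mix any programme effect with that selection, most likely in the programme's favour. The distortion grows as fewer participants are retained, so it should be larger for unguided than for guided. At stake is a supporting result that readers may take as corroboration of the ITT finding, or as the effect of full use.

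**Working it through.** **Step 1: who can be excluded.** The primary endpoint is at about eight weeks, and controls get the programme only after one year.

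| Arm | What could count as not conforming | Documented route before the primary endpoint |
|---|---|---|
| Guided | Not doing the sessions | Yes |
| Unguided | Not doing the sessions | Yes, expected to be more common |
| CAU | Using the programme | None described |
| CAU | Using too much or too little usual care | None, as no content is set |

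A session threshold defined in the SAP would apply only to the arms that have sessions, so it would not remove the asymmetry.

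**Step 2: the yardstick.** The protocol gives no figure for the per-protocol analysis. The comparison value is the planned d = 0.25, with 84 per arm and 252 in total. That total reproduces with a group-by-time repeated-measures F test: three groups, f = 0.125 (half of d), and two measurements with correlation 0.5 (both assumed). The noncentrality is 252 × 0.125² × 2 / (1 − 0.5) = 15.75, and the power is 0.951 against the stated 0.95. The present point does not depend on this calculation.

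**Step 3: size of the selection shift.** Inputs, all assumed because the documents give none:

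- true effect zero;
- share p of an active arm retained: 0.4 (taken for unguided) and 0.7 (taken for guided);
- correlation r between the tendency to adhere and a better outcome, after baseline covariates: 0.1 to 0.3.

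If the tendency to adhere is standard normal and the top share p is kept, its mean among those kept is φ(z)/p, where z is the (1 − p) quantile. The spurious difference from an unselected control arm is r × φ(z)/p in SD units.

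- p = 0.4: z = 0.253, φ(z) = 0.386, φ(z)/p = 0.966
- p = 0.7: z = −0.524, φ(z) = 0.348, φ(z)/p = 0.497

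The false-positive rate uses a two-sided 5% test with standard error √(1/84 + 1/(84p)). This is 0.204 for p = 0.4 and 0.170 for p = 0.7, taking the SD as 1 in both groups.

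| r | Shift, p = 0.4 | False-positive rate | Shift, p = 0.7 | False-positive rate |
|---|---|---|---|---|
| 0.1 | 0.10 | 8% | 0.05 | 6% |
| 0.2 | 0.19 | 16% | 0.10 | 9% |
| 0.3 | 0.29 | 29% | 0.15 | 14% |

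Only one of the six scenarios (r = 0.3, p = 0.4) reaches 0.25. At p = 0.5 the shifts are 0.08 to 0.24.

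**Step 4: guided against unguided.** If the two arms retain different shares, the shifts do not cancel. With 40% and 70% retained and the same r in both arms, the per-protocol comparison tilts towards unguided by r × (0.966 − 0.497): 0.05, 0.09 and 0.14 SD for r = 0.1, 0.2 and 0.3.

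**The case against.** **The analysis is secondary.** ITT is the main analysis, the trial is a superiority trial, and nothing gives the per-protocol set confirmatory weight. This stands, and it limits how much the point matters.

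**Conforming is not defined in the article, and the SAP may define it.** This stands in part. If conforming means only having been given the assigned condition, few participants are dropped and the analysis is close to ITT. If it means completing sessions, the asymmetry follows whatever the threshold.

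**A control could fail to conform.** The exclusion for taking part in similar studies applies only at inclusion, so a control could later join another online programme, and the service-use questionnaire might show it. A reader might infer that no control can ever be excluded, but the documents do not support so absolute a claim. Occasional cases would still not balance session non-completion in the active arms.

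**The sizes are assumed.** This is true. The planned baseline covariates would also absorb part of the selection, which is why r is defined as the correlation that remains.

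**A reader might infer that the bias threatens the second hypothesis**, on guided against unguided. The documents do not support this. That hypothesis concerns the cost-effectiveness ratio, and the Cost-effectiveness section analyses it by ITT with multiple imputation. The authors also say the sample is too small to compare the two active arms directly.

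**A complier-average estimate has its own weakness.** Sessions 1 and 2 already contain goal-setting and behavioural activation, and guided participants receive individual feedback. If partial use helps, a high threshold overstates the effect among compliers. This stands and shapes the fix.

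**Conclusion.** The point holds as a limited one. The per-protocol contrasts with CAU will not be between randomized groups, because exclusions fall almost entirely on the active arms and probably most on unguided. The likely direction is in favour of the intervention, though that is not certain. Under 40% to 70% retention and a residual correlation of 0.1 to 0.3, the spurious difference is about 0.05 to 0.29 SD. In most of that range it is well below the planned 0.25, and only the least favourable corner reaches it.

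This rests on conforming being judged by programme use, and on the assumed retention and correlation. It does not touch the ITT conclusions or the cost-effectiveness analysis.

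**What to change.** For the question of what the programme does in those who use it, estimate a complier-average causal effect for each active arm versus CAU, with randomization as the instrument and all randomized controls kept. In its simplest form this is the ITT difference divided by the share of the active arm that reaches the threshold. With no true effect it is centred on zero, whatever r is.

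- Pre-specify a low threshold, such as any session started, so that assuming no effect below it is plausible. Show sensitivity to higher thresholds. The platform must already track completion, since the mid-intervention assessment can be triggered by finishing session 5 and reminders by delay.
- Do not read the two complier effects as a comparison of guided with unguided, because the compliers in each arm are different subgroups.
- If the per-protocol analysis is kept, label its contrasts non-randomized and exploratory. Do not use it to support efficacy or to compare guided with unguided.

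The cost is SAP wording and a small amount of analysis, wider confidence intervals, and reliance on the exclusion restriction. With 84 per arm and SD 1, the standard error of the ITT difference is √(2/84) = 0.154. Treating the complier share as known, the complier estimate has standard error 0.154/0.7 = 0.22 at 70% compliers and 0.154/0.4 = 0.39 at 40%, against 0.17 and 0.20 for the per-protocol contrast. A low threshold, which more participants reach, narrows that gap.

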### Cost-effectiveness

Cost-effectiveness will be assessed from a societal perspective for both disorder-free days and QALYs. The analysis will be performed according to the ITT principle. Multiple imputation according to the MICE algorithm developed by Van Buuren et al. [107] will be used to impute missing cost and effect data. Incremental cost-effectiveness ratios (ICERs) will be calculated by dividing the pairwise differences in the mean societal costs between the groups by the pairwise differences in mean effects between the groups. Bivariate regression models will be used to estimate cost and effect differences while adjusting for confounding if necessary. Statistical uncertainty will be estimated using bias-corrected accelerated bootstrapping with 5000 replications. Uncertainty surrounding the ICERs will be presented in cost-effectiveness planes and acceptability curves [108].

## Discussion

The high prevalence and burden of depression and anxiety, both on an individual and societal level, warrant effective and low-threshold prevention strategies. Students are considered an at-risk group for developing these conditions due to their age of onset and the challenges that this population faces [6]. So far, research on the effectiveness of Internet-based prevention in college students is largely limited to the field of eating disorders and substance use [109, 110]. However, scientific evidence on the value of, in particular, transdiagnostic individually tailored interventions for the indicated prevention of depression and anxiety among college students is scarce.

Based on these considerations, we have developed the ICare Prevent intervention. Originally conceived for the indicated prevention in the general population in Germany, we have adapted it to a Dutch college student context. To do that, we have started with a literal translation from German into Dutch. In addition, focus groups have been conducted with students to map out core features that are attractive to them. As a result, the intervention has been shortened considerably while leaving the psychotherapeutic components intact. This was assured by the supervision of a licensed psychotherapist. Moreover, problem descriptions and the testimonials have been changed to represent the diverse student population and their experiences related to study stress, balancing work and studies, as well as dealing with family members, partners, and friends.

### Strengths and limitations

To our knowledge, this is the first trial that investigates the (cost-)effectiveness of a transdiagnostic individually tailored Internet-based intervention for the prevention of depression and anxiety in a college student population. Data on both symptom reduction as well as the time to onset of a mood or anxiety disorder will be measured. Although some research suggests that Internet-based interventions have the potential to be cost-effective compared to no treatment, no data are available for preventive transdiagnostic individually tailored Internet-based interventions for college students. Specifically, the added (economic) value of support by means of an eCoach needs to be closely monitored in the context of this low-intensity intervention.

Some possible limitations of the present trial should be noted. First, the sample size of this trial conducted among Dutch college students is insufficient for directly comparing the guided and unguided treatment arm as well as analyzing the time to a mental health disorder onset. Similarly, analyses of moderators and mediators will be underpowered and may therefore provide only limited insights. To counter this issue, data from all participating trials in the ICare project will be pooled in order to achieve enough statistical power. Second, an evaluation of societal costs might be difficult due to the fact that most students are seldom in full-time employment. The detrimental effect of depression and anxiety on absenteeism and presenteeism in the context of employment is therefore difficult to quantify. In order to increase the validity of the results, we have adapted the cost-effectiveness questionnaire (CSRI; [52]) to fit the specifics of a student population by focusing on absenteeism and presenteeism in student jobs, as well as in lectures. Finally, previous research has shown that adherence to Internet interventions is a point of concern, especially in unguided formats [111, 112]. A series of automatic motivational messages and reminders will be used in order to increase adherence in the unguided study arm and we will closely observe factors related to dropout. This will be beneficial in designing future interventions and improving uptake of intervention content.

## Trial status

Recruitment started in July 2017. Follow-up assessments for the last participant are expected to be completed by 31 August 2019.

## Abbreviations

AES: Advanced encryption standard
AQoL-8D: Assessment of Quality of Life – 8 Dimension version
AUDIT-C: Alcohol Use Disorders Identification Test – Consumption questions
BADS-SF: Behavioral Activation for Depression Scale – Short Form
BFI-10: Big Five Inventory – 10 item version
CAU: Care as usual
CBT: Cognitive behavioral therapy
CD-RISC: Connor Davidson Resilience Scale
CEQ: Credibility/Expectancy Questionnaire
CES-D: Center for Epidemiologic Studies Depression Scale
CSQ-8: Client Satisfaction Questionnaire – 8 item version
CSRI: Client Service Receipt Inventory
ECTS: European Credit Transfer System
EQ-5D-5 L: EuroQol – 5 Dimension – 5 Level questionnaire
GAD-7: Generalized Anxiety Disorder Scale – 7 item version
HTTPS: Hyper text transfer protocol secure
ICER: Incremental cost-effectiveness ratio
INEP: Inventory of Negative Effects of Psychotherapy [Inventar zur Erfassung negativer Effekte von Psychotherapie]
INKK: Incongruence Questionnaire – Short Form [Inkonkruenzfragebogen - Kurzform]
ISO: International Organization for Standardization
ITT: Intention-to-treat
M.I.N.I.: Mini International Neuropsychiatric Interview
MDD: Major depressive episode
NEN: Dutch norm [NEderlandse Norm]
PHQ-9: Patient Health Questionnaire – 9 item version
PSQI: Pittsburgh Sleep Quality Index
PSS: Presenteeism Scale for Students
PSWQ-3: Penn State Worry Questionnaire – 3 item version
QALY: Quality-adjusted life years
QIDS-CR: Quick Inventory for Depression Scale – Clinician Rated
RSA: Asymmetric Encryption Algorithm
SHA-1: Secure Hash Algorithm 1
SIGH-A: Structured Interview Guide for the Hamilton Anxiety Rating Scale
SSL: Secure sockets layer
TEQ: Treatment Expectancy Questionnaire
WAI-SR: Working Alliance Inventory – Self-rated
WHO-5: World Health Organization Ten Well-being Index – 5 item version
